### Interventions

*Criteria for discontinuing allocated interventions for a given trial participant*

If any patients in any of the allocated groups develop any complication (
*e.g.*, deep venous thrombosis), their participation will be discontinued in the study. The patients will then receive appropriate care and offered outpatient rehabilitation as needed. Study participants will be retained in the trial (unless they withdraw their consent) to enable follow-up data collection and to prevent missing data.

*Adherence and concomitant care*

During the first consultation, the importance of following the study guidelines and adhering to the allocated group will be highlighted. Exercise adherence will be recorded as a percentage of completed exercises during the first follow up (after the six-week intervention) for both groups. Exercise adherence will be taken into consideration when performing the pre-protocol analysis.

All enrolled patients will be encouraged to contact the principal investigator directly if experiencing problems related to their allocated group intervention. The principal investigator will then fill out a standardized form at these calls. Patients can use medicines and nutritional products as needed, prescribed by their physician. To avoid study-contamination, patients will be asked to adhere to the allocated rehabilitation intervention and not to seek alternative health-care services during the course of the study. Patients will be advised to contact their general practitioner or the principal investigator as needed.

The physiotherapy intervention will be given to Groups A and B for six weeks. The intervention will be provided for 60 minutes, five days each week. Both Group A and Group B will receive conventional treatment. Group A will receive mCIMT along with the conventional therapy, while Group B will receive the motor relearning program along with the conventional therapy. Treatment will be provided to both groups for six weeks.

*Modified constraint-induced movement therapy (mCIMT)*

Exercises will be given to participants that have a functional focus and will be under supervision. The affected lower extremity will be the focus of these exercises. Based on the desired movements, the therapist (principal investigator) recommended these exercises.

The 30-minute mCIMT approach will consist of the following movements: Transfer package (10 minutes per session), side stepping, ball kicking, stair climbing, and knee control on a step.

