### Data collection methods

Before group allocation, screening of the participants as per the inclusion and exclusion criteria will be carried out. This will be followed by baseline assessment of the outcome measures as mentioned. All participants will undergo the randomization process and are allocated into either group A or Group B. The intervention will be administered for an hour daily, five days per week for six weeks. The post intervention data for the outcomes will be recorded after the last intervention session day. The data will be compiled and analysed for studying the results. The study interventions will be administered by the principal investigator under the supervision of the guide throughout the duration of the study. The patients will be instructed and reminded of the sessions in advance through messages sent to their mobile phones so that adherence to the study is ensured. Furthermore, if the patient misses their sessions due to any reason, the standby days from the week will be utilized such that the patient receives a total of 30 sessions of intervention in the six week duration.

As per in the sample size calculation we have given a 10% dropout rate so that it does not interfere with the results of our study.

The data collection forms can be found as
*Extended data.*
^
24
^

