### Monitoring

*Data monitoring*

We will have a data monitoring committee lead by the PI for maintaining and integrating of the data.

*Harms*

The whole procedure is going to held under the supervision of clinicians and departmental committee During the trial, harms and adverse event will be immediately reported to the committee. The final dataset will be uploaded to the institutional research website and will be accessible to concerned authorities.

*Auditing*

Every month, auditing of the trial is going to be conducted. Any deviation from the protocol will be documented and will be addressed.

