### Ancillary and post-trial care

The whole procedure is going to held under the supervision of clinicians and the departmental committee
*i.e.*, Guide, Head of department, Principal and member of Research Guidance Cell.

After the trial session, the participations are going to be under supervision for about four weeks so that if there will be any harm, the Principal Investigator will take care of the participants.

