## Discussion

The study’s primary objective is to determine how well mCIMT and MRP work to treat balance and gait issues. These cause a rise in the risk of falling, which further reduces the functional independence of those who had sub-acute stroke. In a previous study, the experimental group received mCIMT for two weeks, while the control group received neurodevelopmental therapy (NDT). The findings showed that mCIMT for lower limb had a superior impact on improving motor function compared with NDT.
^
22
^ Using a randomized controlled trial, the study was done to determine how well the MRP worked to improve balance and upright mobility in sub-acute stroke patients. The results suggested that MRP showed a good impact on post-stroke survivors with the experimental group receiving MRP in addition to conventional physical therapy (RPT) for a duration of five days per week for eight weeks.
^
23
^ Both interventions were found to be beneficial in hemiplegic stroke when compared with a negative control group. But there is dearth of literature reflecting the superiority of either of these interventions when compared with each other. Therefore, our study will compare the two regimes to evaluate which is more successful while looking at the effectiveness of these therapies in sub-acute stroke patients.

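### The only recording form described for problems depends on patients calling about treatment-related problems, while the Harms section promises reporting of all harms without saying how they are found

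*Protocol article*

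**What the plan says.** Four parts of the protocol article bear on how problems are found and recorded.

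- **Interventions, Adherence and concomitant care.** "All enrolled patients will be encouraged to contact the principal investigator directly if experiencing problems related to their allocated group intervention". The next sentence gives the recording step: "The principal investigator will then fill out a standardized form at these calls". Later in the same subsection there is a wider invitation: "Patients will be advised to contact their general practitioner or the principal investigator as needed". No recording step is attached to it. The discontinuation criteria just before this subsection make any complication a reason to end participation, without saying how complications are identified.
- **Monitoring, Harms.** "During the trial, harms and adverse event will be immediately reported to the committee". This is not restricted to events thought to be related.
- **Ancillary and post-trial care.** After treatment, "the participations are going to be under supervision for about four weeks so that if there will be any harm" the investigator can take care of the participant.
- **Data collection methods.** The principal investigator delivers the treatment, and missed sessions are made up so that each "patient receives a total of 30 sessions of intervention in the six week duration".

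The trial is open label with no blinding. The Discussion says of balance and gait problems: "These cause a rise in the risk of falling". The listed outcomes include the Fall Efficacy Scale, which measures fear of falling. Falls themselves are not a listed outcome.

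**The concern.** The described recording step passes through two filters. The patient must start the contact, and the contact is invited for problems linked to the allocated programme, so the patient makes the first judgement of cause. The Harms section promises something wider than this step can supply.

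Falls show the gap most clearly. The protocol cites fall risk when explaining why balance and gait matter. Both programmes have patients with impaired balance practise demanding tasks: stair climbing and side stepping in one, tandem or one-leg standing and cross-over stepping in the other. A fall at home that the patient puts down to a wet floor or to the stroke itself does not fit the invitation to call.

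Two things are at stake. One is a complete description of harms for those who would later use either programme. The other is even-handedness: patients know which programme they receive, and the two programmes contain different tasks, so the readiness to blame the programme, and hence to call, could differ between arms.

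**Working it through.** **Step 1: the passages side by side.**

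| Place | Who starts it | Limited to related problems? | Recording step described? |
|---|---|---|---|
| Interventions: call about the allocated intervention | Patient | Yes | Yes, the standardised form |
| Interventions: contact as needed | Patient, possibly to the general practitioner | No | No |
| Interventions: complication leading to discontinuation | Not stated | No | No |
| Monitoring, Harms: report to the committee | Not stated | No | Onward reporting only |
| Post-trial care: about four weeks of supervision | Not stated | No | No |

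Only the first row has both a way for a problem to come to light and a form on which to write it down, and that row is the narrowest in scope. The others provide contact, reporting or oversight.

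**Step 2: the number of contacts.** Five days a week for six weeks gives 5 × 6 = 30 sessions, which agrees with Data collection methods. With 34 patients this is up to 34 × 30 = 1,020 planned contacts with the treating investigator. The article describes no structured question about events at any of them.

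**Step 3: illustration of size.** The documents give neither an event risk nor a capture rate, so both are assumed here. Let p be the risk that a patient has at least one event in six weeks, c the share of affected patients who are recorded, and n = 17 per arm (from the Methods). With independent patients:

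- expected recorded patients per arm = n × p × c
- chance of at least one recorded patient in an arm = 1 − (1 − p × c)^17

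| p (assumed) | Full capture, c = 1 | c = 0.5 | c = 0.25 |
|---|---|---|---|
| 5% | 0.85 expected; 58% | 0.43; 35% | 0.21; 19% |
| 10% | 1.7; 83% | 0.85; 58% | 0.43; 35% |
| 20% | 3.4; 98% | 1.7; 83% | 0.85; 58% |

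For example, at p = 10% and c = 0.5: 1 − 0.95^17 = 1 − 0.418 = 0.582. The table shows how sensitive a small arm is to incomplete capture. It does not estimate what this trial will miss.

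**The case against.** The case on the other side has real force on several points.

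- **The quoted sentence is not labelled as the harms procedure.** It stands under adherence, and Harms has its own heading. That is correct. But the Harms section says only that "harms and adverse event will be immediately reported to the committee". It gives no means of finding the events, so the call-and-form step is the only concrete one the article offers.
- **There are other routes.** A reader might infer that a patient's call is the trial's only route for harms, or that a fall could be recorded only if the patient both blames the programme and calls. The documents do not support that. The committee report, the as-needed contact, the complication rule and the post-trial supervision are not filtered by cause, and nothing confines the recording of all harms to calls.
- **Events may surface anyway.** A reader might also infer that falls will be missed. That is too certain. The investigator treats each patient in person 30 times, would witness events in sessions and may hear of others. Such noticing is not described as structured or documented, so the risk of under-ascertainment remains.
- **The article is condensed.** The data collection form and the assessment schedule are extended data not shown here. It cannot be said that nothing is asked at the sessions, only that no question is described. If the form already contains a harms item, the article's text should be aligned with it.
- **The inputs in the illustration are invented.** This stands, which is why a range is given. With 20% risk and 90% capture, the chance of seeing no affected patient in an arm is 0.82^17 = 3.4%, against 0.80^17 = 2.3% with full capture. If capture is nearly complete, little is lost.
- **A safety comparison is not an objective and would be weak anyway.** This also stands. Even 3 of 17 against 9 of 17 gives a two-sided Fisher p of 0.07. The case for change rests on complete and even-handed description.
- **Both arms have the same therapist, schedule and instructions.** True, so uneven reporting is a possibility and not a demonstrated bias. It arises because patients know their arm and the filter relies on their own attribution.

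**Conclusion.** The point holds in a limited form. The article states a passive, attribution-filtered recording step in one section and a promise to report all harms in another, and it does not connect the two. Harms the patient does not link to treatment, falls at home above all, may be under-ascertained, possibly to a different degree in the two arms. The amount cannot be estimated from the documents. With half of affected patients recorded, the loss in the chance of seeing any affected patient in an arm of 17 is about 15 to 25 percentage points for assumed risks of 5% to 20%. With near-complete capture it would be small.

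The conclusion rests on what the article describes and would weaken if the unseen data collection form already asks about events at each visit. It does not touch the primary outcomes. The change is worth making because it is cheap and the study had not begun when the article was written.

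**What to change.** Reconcile the Interventions and Harms sections. Suggested text for both:

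*At every treatment session and at the six-week assessment, the therapist asks one fixed open question, in the same wording in both groups, about falls and any other new events since the last contact. The standardised form is completed for every event, whatever its presumed cause. Patients may also report events by telephone at any time. Events are reported descriptively by group, as the number of patients with at least one event and as the total number of events.*

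The telephone route stays as an addition. The change concerns data collection and reporting only, and no formal between-arm safety test is implied.

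Cost: if the question takes about a minute (an assumption), 30 sessions add about 30 minutes per patient, or 1,020 minutes (17 hours) over 34 patients, plus one further minute each at six weeks. No extra visits or staff are needed. More events will be recorded and passed to the committee, so its workload will rise somewhat, and the form may need an item for events judged unrelated.

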### Outcome measures

Time frames at baseline and six weeks later.

*Primary outcomes*
1.
Change in Berg Balance Scale (BBS)
The BBS is a scale with 14 items that is frequently used and is a standardized balance assessment that uses observation to quantitatively assess a patient’s capacity for balance, either statically or while engaging in a variety of planned routine daily tasks. For evaluating static and dynamic balance following a stroke, The inter-rater and intra-rater reliability of BBS for the patients with stroke is 0.97 and 0.98, respectively.
^
15
^ Each item on the scale will be given a score between 0 and 4, giving the patient an overall ranking of 56. A score of 0 means you didn’t complete the project, and a score of 4 means you did it independently.
^
16
^
2.
Change in Dynamic Gait Index (DGI)
The goal of the DGI is to examine dynamic balance while in motion. Eight of the tasks ask participants to keep their balance when walking normally and while doing so in various conditions (such as adjusting their speed, turning their heads to go around obstacles, pivoting around and climbing steps). Each item is given a score between 0 and 3 points, with a maximum score of 24. A higher DGI score indicates greater independent functional mobility. The DGI has been shown to yield ratios of subject variability to total variability with excellent interrater reliability 0.96 and test-retest reliability 0.98.
^
17
^

*Secondary outcomes*
1.
Change in Trunk Impairment Scale (TIS)
The TIS assesses post-stroke trunk movement, static and dynamic sitting balance, and trunk movement coordination. The TIS is used to analyse motor dysfunction of the trunk after a stroke, static and dynamic seated balance and coordination of trunk movement. Overall reliability for clinical care and research in the TIS, 0.96.
^
18
^
2.
Change in Functional Reach Test (FRT)
Utilising a yardstick fastened to the wall at the acromion’s height, functional reach is determined. Functional reach has been shown to exhibit test-retest reliability, interobserver consistency, criterion validity, and concurrent concept validity in earlier investigations. Additionally, it has been demonstrated that in patients undergoing rehabilitation, functional reach is sensitive to clinically significant changes in balance.
^
19
^
3.
Change in 10 Meter Walk Test (10MWT)
Ambulation speed is a crucial component of gait and is frequently utilised in clinical and research settings as an objective indicator of functional mobility. In healthy older adults, gait speed can also be determined using the 10MWT. Therefore, to obtain the most accurate clinical evaluation of walking speed, we advise performing the 10MWT.
^
20
^
4.
Change in Fall Efficacy Scale (FES)
The FES International, a tool designed to measure patient’s fears about falling, has strong psychometric qualities. The 16 items on the Persian FES were factor analysed. The Persian FES showed outstanding test-retest reliability, according to the results. In stroke patients, FES showed that the assessment of fear of fall was appropriate and acceptable. Concerns of falling during physical and social activities could be addressed using the FES. Additionally, it can be applied in a clinical context to identify individuals who have a fear of falling.
^
21
^

### Sample size calculation

We estimated the sample size using a power analysis with 80% power and 5% Type 1 error for the main variables. The BBS score, in comparison to the difference in mean score pre and post treatment for mCIMT group from baseline to end visits. For the study, we used the previously determined effect size difference in percentage from the RCT.
^
22
^ Formula using mean difference:

$$n1=n2=2\frac{{\left(Z_{\alpha }+Z_{\beta }\right)}^{2}\sigma^{2}}{{\left(\delta \right)}^{2}}$$
Primary Variable (BBS)

Mean ± SD (Pre) result on BBS for mCIMT = 48.8 ± 4.7

Mean ± SD (Post) result on BBS for mCIMT = 52.5 ± 3.5

Difference = 3.7

Pooled std. dev. = (4.7 + 3.5)/2 = 4.1

$$\text{N1}=2^{*}\left[{\left(1.64+0.84\right)}^{2}{\left(4.1\right)}^{2}\right]/{\left(3.7\right)}^{2}=15$$

Considering 10% dropout = 2

Total samples required = 15 + 2 = 17 per group.

Total sample size required = 15

Notations:

$$Z_{\alpha }=\text{1.64 bat 5\% l.o.s. at both sides total 10\% type I error}$$

α=Type I error at 5%

$Z_{\beta }=0.84\;\left(1-\beta \right)=\text{Power at}\;80\%$

σ=std.dev=0.5pooledstd.dev

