**Conclusions:**

There is sufficient evidence to derive the conclusion that the functional mobility and balance of stroke victims can be improved with physiotherapy. Therefore, this study will try to seek the comparison of mCIMT (group A) and MRP (group B) in sub-acute stroke subjects and compare the two regimes to determine which one will be superior.

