### Statistical analysis

Samples taken in accordance with the protocol and recorded on a basis that includes all relevant characteristics. Dataset of outcome variables including demographic, physical, laboratory and vitals information will be collected and tabulated in Excel, and will be analysed using R-Software version 4.3. Demographic variables such as age and gender and physical examination (height, weight, BMI), laboratory parameters (haemoglobin, Erythrocyte Sedimentation Rate (ESR), Liver Function Test (LFT), Kidney Function Test (KFT)), and vitals (respiratory rate, pulse rate, systolic blood pressure, diastolic blood pressure and SpO
_2_ levels) will be collected. Outcome variables such as BBS, DGI, TIS, 10MWT, FRT and FES will be presented over descriptive statistics with categorical tabulation for frequency and percentage, while quantitative measurements with minimum, maximum, mean and standard deviation.

The primary outcome variables will include the BBS for measuring balance and the DGI for measuring gait outcome variables, the secondary outcome variables include the TIS, FRT, 10MWT and FES. Variables as primary and secondary parameters for their measuring assessment at different time visits will be assessed to find the significance in mean at 5% level of significance at P-value < 0.05. Statistical analysis will be performed for hypothesis testing for paired pre and post analysis using a paired t-test for normal data or non-parametric test such as Wilcoxon signed-rank test for non-normal data. Similarly, an unpaired t-test will be used for two independent groups for the change in parameters readings of primary and secondary variables at two different visits.

Data over the outcome variables will be analysed for normality (normal distribution) using Kolmogorov–Smirnov test. If data results over non normal distribution then alternate non parametric test will be used.

Confounding variables will be analysed with generalised linear model to find the random and fixed effects over the outcome variables. Association analysis for finding significance of cofounding parameters will be examined by using Chi-squared test or Fisher’s exact test or by using multi-variant analysis.

Full analysis set for the values of outcome variables will be analysed for the results missing data will be covered with imputation method by calculating the mean and median over the existing data.

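### The sample size is labelled 5% type I error but uses the multiplier for 10% two-sided; read as a two-sided 5% test, the printed inputs give about 67–72% power by t-test, not 80%

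*Protocol article*

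**What the plan says.** All of the following is in the protocol article.

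- **Sample size calculation, opening sentence:** "We estimated the sample size using a power analysis with 80% power and 5% Type 1 error for the main variables".
- **Sample size calculation, inputs:** "Difference = 3.7", taken from the pre and post Berg Balance Scale means of the mCIMT group in an earlier trial, and "Pooled std. dev. = (4.7 + 3.5)/2 = 4.1". The formula is the normal-approximation formula for two means, with multipliers 1.64 and 0.84. It gives 15 per group, to which 2 are added for 10% dropout, making 17 per group.
- **Sample size calculation, notations:** 1.64 is glossed as 5% "l.o.s. at both sides total 10" per cent. The next line gives "α=Type I error at 5" per cent.
- **Sample size calculation, closing total:** "Total sample size required = 15", directly after the line that gives 17 per group. The Methods (Protocol) section enrols 34.
- **Statistical analysis:** primary and secondary variables "will be assessed to find the significance in mean at 5% level of significance at P-value < 0.05". The two groups are compared by an unpaired t-test on change, or by a non-parametric test if the data are not normal. Neither one-sided nor two-sided is stated.
- **Abstract, Conclusions:** the trial will "compare the two regimes to determine which one will be superior". The Discussion puts the same undirected question.

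**The concern.** The section gives two values for the total type I error, 5% and 10%, and the arithmetic follows the second. The analysis then declares significance at P < 0.05. If that is an ordinary two-sided test, the trial was sized for a more lenient criterion than the one it will apply, and the advertised 80% power is overstated.

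This matters for interpretation. With about 67% power, the chance of missing the assumed difference is about one in three, not one in five. In a comparison of two active regimens, a non-significant result could then be misread as showing that they are equally good.

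**Working it through.** **Inputs.** Difference δ = 3.7, SD σ = 4.1, multipliers 1.64 and 0.84, 15 evaluable and 17 enrolled per arm (Sample size calculation); P < 0.05 and an unpaired t-test on change (Statistical analysis).

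**1. Reproduce the plan's figure.** n = 2(Zα + Zβ)²σ²/δ²

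= 2 × (1.64 + 0.84)² × 4.1² / 3.7² = 2 × 6.1504 × 16.81 / 13.69 = 15.10.

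The plan prints 15; rounding up would give 16. Allowing for 10% dropout, 15/0.9 = 16.7, so 17. The printed figure is therefore reproduced, with 1.64.

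**2. What 1.64 stands for.** The upper tail of the normal distribution beyond 1.64 is 0.0505, so both tails together hold 0.101. This agrees with the notation's total of 10% and not with the 5% in the opening sentence, unless the test is one-sided.

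**3. Same formula at two-sided 5%.** 2 × (1.96 + 0.84)² × 16.81 / 13.69 = 2 × 7.84 × 16.81 / 13.69 = 19.25, so 20 per arm.

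**4. Power at the planned size.** The standard error of the difference is σ√(2/n).

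- n = 15: 4.1 × √(2/15) = 1.497; 3.7/1.497 = 2.471. Normal approximation: Φ(2.471 − 1.96) = Φ(0.511) ≈ 0.695.
- n = 17: 4.1 × √(2/17) = 1.406; 3.7/1.406 = 2.631. Normal approximation: Φ(0.671) ≈ 0.749.

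The t-test column uses the noncentral t distribution with 2n − 2 degrees of freedom and the same noncentrality.

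| Evaluable per arm | Two-sided 5%, t-test | Two-sided 5%, normal | One-sided 5%, t-test |
|---|---|---|---|
| 15 | 66.5% | 69.5% | 77.8% |
| 17 (no dropout) | 72.3% | 74.9% | 82.4% |
| 20 | 79.4% | 81.4% | – |
| 21 | 81.4% | – | – |

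So 80% power at two-sided 5% needs 21 per arm by the planned t-test and 20 by the protocol's normal formula. With 10% dropout that is 21/0.9 = 23.3, so 24, or 20/0.9 = 22.2, so 23, against the planned 17.

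**5. Sensitivity to the SD.** Pooling by root mean square gives √((4.7² + 3.5²)/2) = 4.14 and t-test power of 65.6% (n = 15) and 71.4% (n = 17), which is little different.

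The planned test, however, is on change. The SD of change is √(4.7² + 3.5² − 2ρ × 4.7 × 3.5), and the protocol does not give the pre–post correlation ρ. Assuming ρ = 0.5, 0.6 or 0.7, the SD is 4.23, 3.82 or 3.36, and two-sided t-test power at 15 per arm for a difference of 3.7 is 64%, 73% or 83%.

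**The case against.** **The test might be one-sided.** The Statistical analysis section does not state sidedness. At one-sided 5%, t-test power is 77.8% with 15 per arm and 82.4% with 17, so the claim of 80% would roughly hold. This stands to the extent that two-sidedness is inferred, not written. The inference is strong: no one-sided test is declared, the notation itself speaks of both sides, and the question names no favoured arm. Calling the trial a superiority trial does not supply a direction between two active regimens. Even on the one-sided reading, the notation's total of 10% contradicts the 5% stated around it and would need correction.

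**The powers do not describe this trial.** This also stands. The 3.7 is the pre–post change within one arm, not a difference between mCIMT and MRP, and 4.1 averages two cross-sectional SDs. A reader might infer from the table that the trial's real power to separate the regimens is 67–72%. The documents do not support that: they give neither a between-arm difference nor an SD of change. The percentages check the printed calculation and nothing more.

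**The remaining slips are minor.** Agreed. Rounding 15.10 down costs one participant per arm, and the total of 15 is evidently a slip, since 17 per group and 34 overall stand elsewhere. Neither adds to the weight of the point.

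**Conclusion.** The point holds in this form. The sample size section contradicts itself on type I error, and its result follows from the 10% two-sided multiplier. Read as a two-sided 5% test and taking δ = 3.7 and SD = 4.1 as printed, power is about 67% with 15 evaluable per arm and 72% with 17 by the planned t-test, or about 70% and 75% by the normal formula. The shortfall from 80% is between 5 and 13 percentage points, depending on method and dropout.

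A reader might go further and say that the stated power and stated alpha cannot both hold under any reading. That is too strong: a declared one-sided 5% test would come close to 80%. What is certain from the text alone is the 5% against 10% contradiction; the size of the shortfall rests on the two-sided reading and on the printed inputs.

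**What to change.** In the Sample size calculation section:

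1. State that the test is two-sided at 5%, and say the same in the Statistical analysis section.
2. Replace 1.64 by 1.96, delete the remark that the total type I error is 10%, and round up.
3. Restate the result without mixing methods, for example:

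> For a difference of 3.7 and an SD of 4.1 at two-sided 5%, 80% power needs 21 evaluable participants per arm by t-test (20 by the normal formula). The planned 17 per arm (15 evaluable) gives about 67% power by t-test, or 72% without dropout (70% and 75% by the normal formula). These figures are conditional on the inputs shown: 3.7 is a pre–post change within one arm, and 4.1 is not the SD of change.

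4. Replace the closing total of 15 by 34.

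This changes text only. The cost is a less favourable power statement. The Study status section says that the study has not begun, so the correction can precede enrolment. The Protocol amendments section says that no further changes could be made, but that is no reason to leave an incorrect power statement uncorrected. Enrolling more participants (23 to 24 per arm with 10% dropout, on these inputs) is a separate decision and would first need a justified between-arm difference and SD of change.

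### The stated 80% power covers both primary outcomes, but only the Berg Balance Scale was used to size the trial, so the claim is unsupported for the Dynamic Gait Index

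*Protocol article*

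**What the plan says.** The Sample size calculation section opens by attributing "80% power and 5% Type 1 error for the main variables" to the estimate. The text that follows turns to one outcome, and to one arm of a cited trial: "The BBS score, in comparison to the difference in mean score pre and post treatment for mCIMT group from baseline to end visits". The worked calculation is headed "Primary Variable (BBS") and its inputs are:

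- Before treatment, in that arm of the cited trial: "Mean ± SD (Pre) result on BBS for mCIMT = 48.8 ± 4.7"
- After treatment, in the same arm: "Mean ± SD (Post) result on BBS for mCIMT = 52.5 ± 3.5"
- Taken as the effect to detect: "Difference = 3.7"
- Taken as the spread, by averaging the two SDs: "Pooled std. dev. = (4.7 + 3.5)/2 = 4.1"

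These give 15 per group, raised to 17 for 10% dropout. The notation in the same section gives a Z of 1.64 and describes it as a total type I error of 10%.

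Outcome measures lists two primary outcomes, change in BBS and change in DGI. Statistical analysis repeats this: "The primary outcome variables will include the BBS for measuring balance and the DGI for measuring gait outcome variables". It makes the 10 Meter Walk Test secondary and sets significance at P < 0.05.

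**The concern.** A plural power claim in a trial with exactly two primary outcomes will naturally be taken to cover both, yet the calculation shown contains nothing about DGI. The article does not say that DGI was checked, or that BBS was the more demanding of the two.

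What is at stake is how a DGI result would be read. The third objective compares the two therapies on balance and on gait, and the Discussion says the study will judge which regime is more successful. If DGI is not significant, a reader who relies on the power statement may conclude that a trial with 80% power found no gait difference. The sizing gives no basis for that reading.

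The point is confined to the power claim for DGI. It is separate from the type I error of testing two primary outcomes, and from the weaknesses of the BBS calculation itself.

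**Working it through.** **1. Reproduce the protocol's figure.** Inputs, all from Sample size calculation: Z values 1.64 and 0.84, SD 4.1, difference 3.7.

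n per group = 2 × (1.64 + 0.84)² × 4.1² / 3.7² = 2 × 6.1504 × 16.81 / 13.69 = 15.10

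The protocol states 15, and 15 + 2 = 17 per group. The figure reproduces, and every outcome input in it is a BBS value.

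**2. Look for DGI inputs.** Outcome measures gives the DGI's items, range and reliability. Neither that section, Sample size calculation nor Statistical analysis gives a DGI mean, difference, SD or effect size. No DGI power can therefore be calculated from the document.

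**3. Ask what DGI effect the design could detect.** This needs no DGI data if it is expressed in SD units of DGI change. For an unpaired t-test with 15 completers per arm (28 degrees of freedom), power follows from the noncentral t distribution with noncentrality d × √(15/2), where d is the standardised between-arm difference. Solving for 80% power:

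| Level | Critical t | d needed |
|---|---|---|
| Two-sided 10% (Z = 1.64) | 1.70 | 0.93 |
| Two-sided 5% (P < 0.05) | 2.05 | 1.06 |

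The normal approximation, d = (Zα + Zβ) × √(2/15), gives slightly smaller values: 0.91 and 1.02.

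**4. Test the most natural defence, that DGI behaves like BBS.** The BBS effect assumed in the protocol is 3.7 / 4.1 = 0.90. If DGI had the same standardised effect, the noncentrality would be 0.90 × √7.5 = 2.47, and power with 15 per arm would be about 78% at two-sided 10% and about 66% at two-sided 5%. So even a DGI effect as large as the one assumed for BBS reaches only roughly 80% at the 10% level, and falls well short at the level stated for the tests.

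**5. Illustration only.** The document gives no DGI effect, so these standardised differences are assumed. With 15 per arm, by the same t calculation:

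| Assumed d for DGI | Power, two-sided 10% | Power, two-sided 5% |
|---|---|---|
| 0.5 | 38% | 26% |
| 0.6 | 48% | 35% |
| 0.7 | 59% | 46% |
| 0.8 | 69% | 56% |

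These rows show how strongly power depends on an input that the protocol does not supply. They do not estimate the trial's actual DGI power.

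**The case against.** Three arguments run the other way.

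First, the case leans on one plural. The protocol's usual term is primary outcomes, not main variables; the next sentence is a fragment about BBS that reads as a continuation; and the calculation is headed with a single variable. A careful reader can see that BBS was used, and the protocol nowhere names DGI as having 80% power. This is fair as to intent and lowers the seriousness. It does not remove the ambiguity, because two outcomes are called primary elsewhere. If only BBS was meant, saying so costs nothing.

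Second, sizing on one of two primary outcomes is common, and a condensed article may leave the justification to a fuller document. That would answer a complaint about a missing justification. It does not answer this point, because the article makes a positive power claim and displays the calculation offered for it, and the claim is wider than the calculation.

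Third, any figure for DGI power rests on assumed values. This stands. A reader might infer that DGI is underpowered, or that the design does not provide 80% power for gait. The document supports neither inference: without a DGI difference and SD, the true power could lie on either side of 80%. A reader might also infer that DGI is safe as long as its effect matches the one assumed for BBS. Step 4 of the working shows that this is not so either.

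**Conclusion.** The point holds in a limited form: the claim of 80% power at 5% type I error is broader than the calculation behind it and is unsupported for DGI, the only primary gait measure. It is not shown to be false.

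In size, DGI would need a standardised between-arm difference of about 0.93 (two-sided 10%) or 1.06 (two-sided 5%) for 80% power. Both are demanding for a comparison of two active therapies that are each added to the same conventional therapy. The thresholds rest on 15 completers per arm, an unpaired t-test on change, and equal variances; they use no assumed DGI data.

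The consequence is one of interpretation, and the correction is to wording, so this is a modest point. The study is described as not yet begun, so the statement can still be put right before any result is known.

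**What to change.** In Sample size calculation:

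- State that the sample size was calculated on BBS only and that the trial was not sized for DGI.
- Give the DGI difference detectable with 80% power from 15 completers per arm, about 1.06 SD of DGI change at two-sided 5%, so that a non-significant DGI result is not taken as a well-powered finding of no gait difference.
- Do not simply replace the plural with BBS. That would re-assert 80% power at 5% for BBS, while the same section uses Z = 1.64 for a total error of 10% and Statistical analysis tests at P < 0.05. Reconcile those two levels first, then state the BBS power that results.

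Alternatively, if a sourced DGI difference and SD can be found, add a DGI calculation and take the larger of the two sample sizes; that route could raise the number of patients.

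The wording change needs no extra patients. Its only cost is a less favourable power statement, covering one primary outcome instead of two.
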